## Abstract

**Background:**

Young adults are experiencing rising levels of mental health concerns and low well-being, which is exacerbated for around 20% of the population who are high in sensory processing sensitivity (SPS), a distinguishable, partly heritable trait associated with poorer mental health. However, despite this worrying increase in mental health issues among young adults, individuals who score highly on beauty appreciation tend to enjoy better well-being and improved mental and physical health. Several studies have shown that beauty appreciation can be taught and may serve as a cost-effective and enjoyable intervention strategy that can be easily implemented.

**Methods:**

This study has two main aims: (1) to evaluate the effectiveness of an art-based beauty appreciation intervention on enhancing beauty appreciation (primary outcome), and (2) to determine whether increasing beauty appreciation has a causal effect on reducing psychological distress and increasing mental well-being (secondary outcomes) when compared to an active matched control condition designed to isolate beauty appreciation skill development. To assess this, we will conduct a mixed-method randomised controlled trial (RCT) across three measurement points: enrollment, post-intervention, and a 4-week follow-up. *N* = 114 young adults, including those high in SPS, will be blinded and randomly allocated to the intervention or control group (~ *N* = 57/group). Our primary hypothesis is that the intervention condition will exhibit higher levels of beauty appreciation compared to the control group at the post-test while accounting for baseline differences. Our secondary hypotheses address mental well-being and psychological distress. A follow-up analysis will assess if individuals with high SPS can especially benefit and qualitative analysis will address mechanisms, barriers and facilitators between intervention and control, as well as in a high SPS subgroup.

**Discussion:**

The study aims to provide evidence that beauty appreciation skills specifically can lead to increased well-being and decreased psychological distress by including an active matched control condition that isolates this skill development. Based on positive results, the evidence will support the implementation of such interventions for young adults and highly sensitive individuals, which would be widely accessible and easy to incorporate into day-to-day life.

**Trial registration:**

ClinicalTrials.gov Registry Number: NCT06788496 (2024-12-22).

## Administrative information

Note: the numbers in curly brackets in this protocol refer to SPIRIT checklist item numbers. The order of the items has been modified to group similar items (see http://www.equator-network.org/reporting-guidelines/spirit-2013-statement-defining-standard-protocol-items-for-clinical-trials/).

## Introduction

### Background and rationale {6a}

The industrialised world is increasingly stimulating for young adults. Bright 24-h lights, constant traffic noise, strong influences from social media, and an inundation of conflict in the news are now the norm rather than the exception. Although humans have adapted to this increasingly overstimulating world, individuals also vary. Young people, and especially university-age students, are at the brunt of the ever-overstimulating world, with higher levels of mental health issues than ever seen before. A recent study of more than 70,000 Dutch people found that more than half of those aged 16 to 25 have mental health concerns [1].

These effects are further increased for approximately 20% of young adults due to naturally amplified sensitivity to sensory input. This group of “highly sensitive people” is described in the scientific literature as being high on the trait Sensory Processing Sensitivity (SPS). This trait is characterised by increased depth of processing, emotional reactivity and empathy, awareness of the environment's subtleties, and ease of overstimulation [2]. SPS is considered partially distinct from other personality traits [3], is moderately heritable [4], and correlates with broad functional and structural brain networks supporting sensory, cognitive, and emotional processes [5]. Young adults with high scores on SPS appear to be even more at risk for psychological issues [6] with small to medium effect sizes [7, 8]. For example, in a recent Dutch survey, people with high SPS had a three times higher burnout rate than the general population [9]. Furthermore, young adults with heightened sensitivity face an elevated vulnerability to developing mental health concerns [10–12] and report more physical health complaints [13, 14], likely due to overstimulation and lack of emotional regulation skills [11, 12, 14].

One potential avenue that could support young adults’ well-being, including highly sensitive young adults, is the practice of beauty appreciation. Large-scale cross-sectional studies suggest that trait appreciation of beauty may be a protective factor associated with well-being [15–19]. As reviewed by [name] et al. [20], individuals with a higher appreciation of beauty, aesthetic sensitivity, or art-savouring, or a tendency to experience awe exhibit elevated subjective well-being [17, 21], greater life satisfaction [16], reduced depression [22], and improved physical health [15]. Lee et al. [15] also demonstrated predictive validity after accounting for other personality traits, like openness to experience. Notably, aesthetic sensitivity, representing an awareness and appreciation of the environment, is a fundamental part of SPS and those who are more sensitive experience more beauty and awe from the world around them [23]. Many studies suggest that of the facets of the Highly Sensitive Person Scale used to measure SPS [18], aesthetic sensitivity tends to be associated with positive health and well-being outcomes much more than other facets [24]. The past evidence indicates that cultivating an appreciation for beauty could be beneficial for young adults generally, and possibly especially so for young adults with heightened sensitivity.

In addition to studying beauty appreciation as a trait, it can also be studied as a skill. Beyond the above associational data, several experimental studies indicate that one’s tendency to appreciate their environment can also be increased [25–30]. These studies use multi-week paradigms that involve increasing exposure to beauty, teaching awareness of beauty, and reflecting on the worth of beauty. Across these interventions, evaluations of the programmes suggest positive effects. First, compared to baseline or control conditions, significant increases were found in engagement with beauty with large effects [25, 27], and appreciation of beauty [28, 29] and noticing beauty with medium effects [26]. For well-being outcomes, Martinez-Marti et al. [28] found that 97% of the sample qualitatively reported a well-being increase, while Martinez-Marti et al. [29] found significant increases in well-being compared to the control groups with moderate to large effects in a randomised control trial (RCT). However, another study [26] did not see improvements in depression or anxiety between a beauty walk group and a control walk group, possibly due to the small sample size, or more likely due to the single activity used to practice beauty repeatedly.

The link between appreciation of beauty and higher well-being in both the general population of young adults and those high in SPS, as well as previous studies showing the possibility of teaching this skill, raises the question of whether enhancing the propensity to perceive the environment as beautiful could improve well-being and mental health in—and if those high in SPS might particularly benefit from such an intervention.

### Objectives {7}

This study has two main aims: (1) to evaluate the effectiveness of a novel art-based beauty appreciation intervention (ABBA) on increasing beauty appreciation and (2) to determine if increasing beauty appreciation has a causal effect on decreasing psychological distress and increasing mental well-being by comparing these outcomes against a matched control condition which is designed to isolate beauty appreciation skill improvement to only the intervention.

Our intervention goes beyond previous studies by aggregating diverse elements from successful interventions and presenting them in an art-based learning paradigm. Utilising the arts as a tool in education has been widely successful in teaching observation skills and awareness of subtleties in medical education [31]. This study builds upon previous research through a new delivery method, aiming to create an intervention that not only fosters beauty appreciation, but also utilises cultural assets such as artworks and museums as venues to practise beauty appreciation—an activity recognised for its contributions to overall health and well-being [32].

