## Interventions

### Explanation for the choice of comparators {6b}

The intervention and control conditions are described in detail in Table 1, including the intervention goals, activity descriptions, and duration. Both programmes are designed to be progressive curriculums that build upon each day. All intervention programme components were selected based on previous research and have been pilot-tested. The objectives of the intervention programme (see also Table 1) are to help individuals develop an aesthetic mindset, practice observation and appreciation skills, apply these skills to their day-to-day lives, practice emotion regulation with beauty, and incorporate more beauty into their lives. The programme aims to facilitate a gradual transfer of skill from appreciation in art contexts to natural beauty and everyday life. On the other hand, the control programme is designed to match the intervention programme in all aspects except for teaching beauty appreciation and increasing exposure to art and beauty. Past studies [15, 16, 18] have not included control over increased observation skills as a possible confounding factor; instead, other studies have used active control conditions but not matched conditions that truly isolate beauty appreciation as a learned skill or behaviour.

**Table 1 Tab1:** Intervention and control condition programme descriptions

	**Intervention**		**Control**	**Time (mins/day)**
	**Goal**	**Activity description**	**Equivalent activities**	
**Day 1**	Develop Aesthetic Mindset Practice Aes. Mindset and observation skills	4-minute priming video showing a landscape painting that focuses on the brushstrokes, composition, and colour Museum visit with audio guide and reflection about visit. Audio guide asking participants to slow-look at 1–3 artworks and reflect on the meaning and beauty	Priming video about learning to pay attention and being observant in everyday life Visit to be a tourist in their own city or a new city with an audio guide with directions to focus on counting things like pedestrians, types of buildings, details	120
**Day 2,3,4**	Beauty journal about artistic beauty	Written reflection on 3 experiences of beauty that they have encountered that day that is man-made	Journal listing 3 things observed that day	5–10

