**Day 5**	Learning to transfer Aes. Mindset to everyday	Art photography videos focusing on slow and aesthetic looking Beauty Walk	Video of how to focus attention on everyday social interactions and learn about noticing small details Walk to practice observation	20–30
**Day 6,7,8**	Beauty journal	Taking photos or videos of natural beauty they passed during the day	Daily photo journal of descriptive photos of their observations and day life	5–10
**Day 9**	Learning about emotion regulation with beauty	Reading a short text about how beauty can induce positive emotions and with the challenge of reflecting on how beauty has impacted emotions	Reading a text about the importance of observation skills in life, focusing on emotions with the challenge to pay attention to own emotions and aspects of environment that might trigger them	5–10
**Day 10,11,** **12,13**	Practicing emotion regulation with beauty	Daily reflection on how beauty impacted emotions/stress that day. Challenge to stop, find and appreciate beauty when stressed or upset	Daily journal of things that happened that day and how that impacts emotions. Challenge to pay attention to emotions during the day	5–10
**Last day**	Develop beauty seeking behaviour	Making a written plan to add beauty to life. Like taking a trip to encounter beauty or adding beauty to the home	Making a written plan to add something new to their life to continue to practice observation skills	15

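### Aim 2 credits any distress or well-being difference to increased beauty appreciation, but the arms also differ in art exposure, so the planned arm comparisons identify only a programme effect

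*Protocol article*

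**What the plan says.** Objectives {7} states the second aim as to "determine if increasing beauty appreciation has a causal effect on decreasing psychological distress and increasing mental well-being". The means is a comparison of outcomes against a "matched control condition which is designed to isolate beauty appreciation skill improvement to only the intervention". The Methods part of the abstract repeats this aim. The Discussion part of the abstract says the trial aims to show that "beauty appreciation skills specifically can lead to increased well-being and decreased psychological distress", and the main Discussion presents better well-being and lower distress as the consequence of enhanced appreciation.

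The comparator section {6b} says the control matches the intervention "in all aspects except for teaching beauty appreciation and increasing exposure to art and beauty". In Table 1, Day 1 of the intervention is a "Museum visit with audio guide and reflection about visit", while controls take a guided city trip with counting tasks. Section {11d} asks controls not to enter museums on that trip. On Days 10 to 13 the intervention arm receives a "Challenge to stop, find and appreciate beauty when stressed or upset", and the control arm a "Challenge to pay attention to emotions during the day".

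Section {20a} plans an ANCOVA by condition on each post-test outcome, adjusted for baseline, sex and age, and linear mixed models for the longer term. Section {20b} adds the Reliable Change Index, exploratory covariates for factors on which the groups differ, and moderation by sensory processing sensitivity.

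**The concern.** Participants are randomised to a programme, not to a level of beauty appreciation. A statement about the effect of raising appreciation follows from the arm comparison only if appreciation is the sole route by which the programmes can affect DASS-21 and MHC-SF differently. The protocol rests aim 2 on that condition and, in its comparator section, says the condition is not met.

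At stake is what the trial may conclude. If time with art lifts mood without changing trait appreciation on the EBS-R, the arms will differ on DASS-21 or MHC-SF and the aim as worded will be answered wrongly. This matters here because the main Discussion criticises earlier work for causal claims without experimental support and presents the matched control as the remedy.

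**Working it through.** **Step 1. What aim 2 requires.** Let τ be the difference between arms on DASS-21 or MHC-SF. Write τ = τ_app + τ_other, where τ_app acts through increased appreciation and τ_other through anything else that differs between the programmes. Aim 2 reads τ as τ_app, which needs τ_other = 0.

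**Step 2. What differs between the arms.**

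| Element | Intervention | Control | Matched? |
|---|---|---|---|
| Teaching appreciation | Yes | No | No, by design |
| Exposure to art and beauty | Museum visit on Day 1, then beauty-directed tasks | City trip, museums excluded | No, as {6b} says |
| Awareness of emotions, Days 9 to 13 | Text and daily reflection | Text, triggers in the environment, daily journal | Largely |
| Action to take when stressed, Days 10 to 13 | Seek out beauty | None | No, though arguably part of appreciation |

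The first row is the ingredient aim 2 wants to isolate. The second is listed separately from it by the protocol itself, and is enough to break the condition in Step 1. Objectives {7} also links practising appreciation with artworks and in museums to health and well-being. It is not clear whether that credit belongs to the practice or to the setting, so it makes a separate route plausible but does not establish one.

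**Step 3. What the analyses estimate.** The ANCOVA coefficient for condition is τ. The mixed models give the arm contrast over time. The Reliable Change Index compares proportions of responders by arm, and the moderation analysis asks for whom τ is larger. None of these splits τ into τ_app and τ_other. The interviews collect perceived mechanisms and do not estimate a causal link.

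**Step 4. Illustration.** The protocol gives no figure for aim 2, so there is none to reproduce. Take n = 49 per group from the Sample size section, a two-sided 5% test, τ_app = 0 and τ_other = d in SD units. With pre-post correlation r,

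SE = √(1 − r²) × √(2/n), and P(significant) = Φ(d/SE − 1.96) + Φ(−d/SE − 1.96).

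For d = 0.3 and r = 0.5: SE = 0.866 × 0.202 = 0.175, d/SE = 1.71, and P = 0.40.

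| d outside appreciation (assumed) | r = 0.5 | r = 0.72 |
|---|---|---|
| 0 | 5% | 5% |
| 0.2 | 21% | 30% |
| 0.3 | 40% | 57% |
| 0.4 | 63% | 81% |
| 0.5 | 82% | 95% |

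Both d and r are assumptions. The value 0.72 is the beauty scale's retest figure, borrowed here for the distress outcome; 0.5 is a lower alternative. The table is simply the power of the test to detect d. It shows that the test responds to τ_other exactly as it would to τ_app. It does not show that τ_other is this large.

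**The case against.** **The hypotheses are already programme contrasts.** This is correct. H2 and H3 compare the intervention condition with the control, and the ANCOVA matches H2. The fault is confined to the aim and the intended conclusions.

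**The coping practice belongs to the construct.** A reader might count the Days 10 to 13 challenge as a further rival ingredient. The documents do not support that firmly. The section on development of the programmes treats emotion regulation through beauty as a likely mechanism of appreciation, and the Active control description says the control's emotion journalling is meant to match emotional awareness. What remains is that controls receive no comparable action to take. That is a secondary point.

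**Exposure is also part of appreciation programmes.** The development section lists exposure to beauty among the learning outcomes of earlier programmes. This has some weight. But {6b} names exposure apart from teaching appreciation, and aim 2 concerns an increase in appreciation, which exposure need not produce.

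**The pilot supports isolation.** It had three participants per condition on a condensed programme. It bears on whether the control raises appreciation of mundane things, not on whether art exposure has its own effect on mood.

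**No mediation analysis is planned.** A reader might infer this. The article refers to a pre-registration that is not shown and could contain one, so its absence from the article is not a finding.

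**A discordant result would still be reported as an effect of appreciation.** A reader might infer this too. No text says so, and because EBS-R is the primary outcome a discordance would be visible. The article does not, however, say how it would be interpreted.

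**Conclusion.** The concern holds as a contradiction within the protocol. Aim 2 and the conclusions in the abstract and discussion rest on a control that isolates appreciation, while the comparator section says the arms also differ in exposure to art and beauty. The planned comparisons by arm identify the effect of the ABBA programme against the observation programme.

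Nothing here undermines the randomised comparison, H1, H2 or H3. The size cannot be expressed as a share of the effect, because the documents give no basis for dividing it; the percentages above depend entirely on assumed inputs. The conclusion needs only two readings of the text: that aim 2 concerns increased appreciation, and that {6b} means what it says about exposure.

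**What to change.** 1. Restate aim 2, in Objectives {7} and the abstract, as the effect of the ABBA programme compared with the active control on psychological distress and mental well-being. Word the conclusions in the abstract and main Discussion to match. Leave H2 and H3 as they are.
2. State in advance that a DASS-21 or MHC-SF difference without an EBS-R difference will not be interpreted as an effect of beauty appreciation. This rule is necessary but not sufficient: if both differ, appreciation may still not be the cause, which is why item 1 is needed as well.
3. Label any analysis relating T2 EBS-R to later DASS-21 or MHC-SF as exploratory. Appreciation is not randomised, so such an analysis rests on there being no unmeasured confounding. ERS-ACA should not serve as the competing mediator, because its modified stem asks about moments of appreciating beauty. Table 3 shows no art-exposure measure after baseline (two background questions at T3 are not described), so the main rival route could not be modelled.

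The cost is wording, with no change to design, data collection or sample size. The downside is a narrower headline claim.

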### Main hypothesis

H1: The intervention condition will report larger increases in the primary outcome, appreciation of beauty, compared to the control group at the post-test.

H2: The intervention condition will report a larger decrease in the secondary outcome, psychological distress and a larger increase in mental well-being, compared to the control group at the post-test.

H3: The intervention condition will report higher levels of the primary outcome, appreciation of beauty, secondary outcomes: mental well-being, alongside lower levels of psychological distress compared to the control group at follow-up.

Exploratory H4: Sensory processing sensitivity will moderate improvements in both the primary and secondary outcomes.

### Trial design {8}

To evaluate this, we will conduct a mixed-method randomised controlled trial (RCT) with an active control condition assessing the impact of the ABBA intervention on trait appreciation of beauty as a primary outcome and well-being and psychological distress as a secondary outcome. The trial followed a superiority framework. There are three measurement points for the primary and secondary outcomes, including (1) enrollment, (2) a post-test after the intervention/control programme, and (3) a 4-week follow-up measure. *N* = 114 participants will be randomised into either the intervention or control group (~ *N* = 57/group). In addition, to investigate perceived mechanisms, barriers, and facilitators, participants will be selected using purposive sampling and invited to a semi-structured interview until data saturation is reached in both the intervention and control groups, with an additional subgroup analysis on those high in SPS from the intervention group. This qualitative subgroup analysis, combined with a quantitative moderation analysis, will determine whether the intervention is especially effective for those high in SPS.

## Methods: participants, interventions and outcomes

### Study setting {9}

The study is conducted via correspondence (communication through email, Microsoft Teams, online surveys and postal mail, and online-based intervention programme) in the Netherlands.

### Eligibility criteria {10}

Participants must be between 18–28 years of ageIndicate that they have a smartphone to support data collection and programme componentsHave the ability and interest to make a trip to a museum or new location (i.e. new part of the city)Be willing to complete short activities every day for two weeksBe fluent in EnglishBe based in AmsterdamParticipants must not currently be in clinical treatment for a mental health disorder, assessed via self-reportIndicate that they are not currently experiencing severe psychological symptoms (i.e. depression, suicidal ideation, severe anxiety) via self-report

